## Methods/design

This is a study protocol for a randomised controlled trial designed to test the effects of high intensity training compared to low intensity training on anxiety levels.

There will be a random 1:1 allocation into two groups. The two groups are high intensity exercise (1 × 4 minutes performed two times per week with a heart rate of 85–95% of maximal heart rate, corresponding to ≥ 16 on the 6–20 Borg scale) and low intensity exercise (45 minutes performed two times per week with a heart rate of approximately 60% of maximal heart rate, corresponding to 9–11 on the 6–20 Borg scale) [26]. The high intensity group will perform a 10-minute warm-up prior to the high-intensity bout, and a 5-minute cooldown. Due to the low intensity in the low intensity group, a warm-up is not considered necessary.

The total amount of training sessions for both groups will be eight. The high intensity exercise group will serve as the intervention group, while the low intensity exercise group will serve as an active control group.

The trial will be conducted in accordance with the Standard Protocol Items: Recommendations for Interventional Trials statement (SPIRIT) [27].

The trial has been approved by the Data Protection Officer at the University Hospital of North Norway and the Regional Committee on Health Research Ethics (approval number 714458) and registered at ClinicalTrials.gov (Trial registration number NCT06881758).

Participants will provide written informed consent before allocation to the two intervention groups, and they will be randomised into a high-intensity training group and a low-intensity training group, following baseline measures.

Randomisation will be performed using counterbalanced block randomisation in a 1:1 ratio, stratified by sex, to ensure an equal distribution of males and females across the study groups. Block sizes of four–six participants will be used. This will allow for a balanced representation of both genders in each condition. Randomisation will be conducted using a computer-generated random number sequence via the website https://www.randomizer.org/.

Outcomes will be measured immediately after inclusion (baseline), right after the very last exercise session, four weeks after the last exercise session (primary endpoint) and three months after the termination of the intervention period (secondary endpoint) (Fig. 1).

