## Sample size calculation

The sample size calculation of the present study was informed by data from a previous study [21] on psychological effects of high-intensity exercise, which showed a significant reduction in anxiety levels in 33 participants with anxiety disorders. We conducted a power calculation using https://clincalc.com/stats/samplesize.aspx. We assumed a baseline mean of 30 on the Beck Anxiety Inventory (BAI) for each group. The expected post-treatment BAI scores are 14 for the high-intensity group and 22 for the low-intensity group. With a significance level (alpha) of 0.05, SD of 7 and 80% power, the required sample size is 24. This means we need 12 participants per group to detect significant differences using a two-tailed *t*-test. Previous studies have found that the average attrition rate is 20% [33].

To account for an expected attrition rate of about 20% [33], the final target sample size is 30 participants (15 per group), representing the minimum required for adequate power. Additional participants may be included if recruitment permits, to further strengthen statistical power. Potential missing data will be addressed using linear mixed-model analyses, since this analysis is robust to missing-at-random mechanisms. Sensitivity analyses based on both intention-to-treat and per-protocol datasets will be applied to assess the robustness of the findings.

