### Statistical analysis

Data management and analyses are performed using SPSS 30 (SPSS Inc., Chicago, IL, USA). Data will be analysed using descriptive and inferential statistics. Continuous variables are presented with mean ± SD and 95% CIs.

The effect of the intervention will be assessed by examining change scores on the BAI and HADS (primary outcomes) and blood pressure and EKG (secondary outcomes). Changes from baseline to post-tests (immediately, after four weeks, and after three months) will be analysed.

Single measures (e.g. baseline data) will be analysed using ANOVA or linear regression, provided the statistical assumptions for linear models are met. Variables will be assessed for normality through visual inspection of histograms and Q-Q plots, along with a formal test for normality (Shapiro-Wilk test). If the assumption of normality is violated, non-parametric tests will be applied. ANOVA with repeated measures will be used to analyse changes in quantitative data (change scores) and to compare the two groups.

Missing data will be handled using linear mixed-model analyses, which provide unbiased estimates under the assumption that data are missing at random and allow inclusion of all available observations. Furthermore, multiple imputation will be applied as a sensitivity analysis to assess the robustness of the results to potential missingness.

We will also use Bonferroni corrected post hoc comparisons when performing multiple comparisons, ensuring that the overall significance level remains accurate. Additionally, effect sizes are estimated based on Cohen’s *d* (0.2 = small effect, 0.5 = medium effect, and 0.8 = large effect).

Participants with mild-to-moderate depressive symptoms will be eligible for inclusion, as anxiety and depression frequently co-occur in clinical populations. Due to our limited sample size, formal subgroup analyses based on depression status will not be conducted. Instead, the baseline depressive symptom scores (HADS-D) will be entered as a covariate in the statistical models to adjust for their potential influence on anxiety outcomes.

Age will be included as a covariate in all primary and secondary analyses. In addition, exploratory subgroup analyses will be performed by age group (< 40 years vs ≥ 40 years).

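### The stated model adjusts change scores for age and HADS-D but not for the outcome's own baseline or for sex, which gives up some precision in a trial of 30

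*Protocol article*

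**What the plan says.** The Statistical analysis section of the protocol article defines the effect through change from baseline: "The effect of the intervention will be assessed by examining change scores on the BAI and HADS (primary outcomes"), with blood pressure and EKG treated likewise as secondary outcomes. Repeated-measures ANOVA on the change scores compares the groups. Two covariates are named. Baseline HADS-D is entered because of its possible influence on the anxiety outcomes. For age the text is general: "Age will be included as a covariate in all primary and secondary analyses".

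The baseline value of the analysed outcome is not named as a covariate. Nor is sex, although Methods/design says: "Randomisation will be performed using counterbalanced block randomisation in a 1:1 ratio, stratified by sex". A linear mixed model is mentioned for missing data, without covariates and without saying how baseline enters it.

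The same section has a normality rule based on histograms, Q-Q plots and the Shapiro-Wilk test, which ends: "If the assumption of normality is violated, non-parametric tests will be applied".

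**The concern.** Subtracting the baseline is not the same as adjusting for it. A change score fixes the slope of follow-up on baseline at 1. A model with baseline as a covariate estimates that slope and so removes more noise whenever the correlation is below 1. The plan spends covariates on age and a depression score but not on the variable likely to predict follow-up best. It also leaves out the factor that the randomisation balances.

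Precision is at stake. The trial is sized at 12 completers per arm with no reserve, so a chance difference between arms at baseline can move the estimate noticeably.

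The normality rule adds a smaller problem. Standard rank tests take no covariates, so applying them to the primary outcomes would contradict the statement that age is in every primary and secondary analysis.

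**Working it through.** **Inputs from the article (Sample size calculation).** Mean BAI at entry is taken as 30 in both arms, and the means hoped for after training are 14 (high intensity) and 22 (low intensity). On the remaining inputs the article says: "With a significance level (alpha) of 0.05, SD of 7 and 80% power, the required sample size is 24". The comparison is a two-sided t-test with 12 per arm. The difference is 22 − 14 = 8 points. Because both arms start at 30, the difference in change is also 8 (16 against 8).

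**The plan's own figure.** n per arm = 2 × [7 × (1.960 + 0.842) / 8]² = 12.02, which is 12 to the nearest whole number, so 24 in total. With 20% attrition, 24 / 0.8 = 30. The stated figures reproduce. Power at 12 per arm is 79.9% by the normal approximation and 76% by the noncentral t.

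**Variance of the two approaches.** Let r be the correlation between baseline and follow-up. It is not in the article, so 0.3 to 0.7 is assumed, with 7 taken as the SD at each time point.
- SD of change = 7√(2(1 − r)): 8.28, 7.00 and 5.42 at r = 0.3, 0.5 and 0.7.
- SD after baseline adjustment = 7√(1 − r²): 6.68, 6.06 and 5.00.
- Variance ratio, adjusted to change = (1 + r)/2: 0.65, 0.75 and 0.85.

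The change score has the planning SD of 7 only at r = 0.5.

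**Stated model against the fuller model.** The planned model already holds age and HADS-D, so it is the right comparator. Simulation settings: 12 per arm, 8-point effect, normal data, sex balanced within arm, age unrelated to outcome, no sex effect, 3,000 runs per setting (Monte Carlo standard error at most √(0.25/3000) = 0.9 points). The correlation of HADS-D with the outcome's baseline is also assumed.

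| r | HADS-D with baseline | Change + age + HADS-D | Plus baseline and sex | Gain (points) |
|---|---|---|---|---|
| 0.3 | 0.3 | 61.1% | 74.1% | 13.0 |
| 0.3 | 0.5 | 61.4% | 73.7% | 12.3 |
| 0.3 | 0.7 | 65.0% | 72.5% | 7.5 |
| 0.5 | 0.3 | 72.8% | 80.3% | 7.5 |
| 0.5 | 0.5 | 74.2% | 79.7% | 5.5 |
| 0.5 | 0.7 | 77.6% | 80.5% | 2.9 |
| 0.7 | 0.3 | 90.8% | 91.9% | 1.1 |
| 0.7 | 0.5 | 90.8% | 91.9% | 1.1 |
| 0.7 | 0.7 | 92.2% | 92.7% | 0.5 |

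**The part due to sex.** At r = 0.5 and HADS-D correlation 0.5, with an assumed 4-point sex effect on follow-up, power is 71.6% for the stated model, 78.3% with baseline added and 81.0% with sex added as well. With no sex effect, adding sex costs at most 0.9 points in any setting. With no treatment effect and the 4-point sex effect (8,000 runs), type I error is 4.0% for the stated model and 4.8% with baseline and sex.

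**Chance imbalance.** The standard error of the baseline difference between arms is 7√(2/12) = 2.86 points. An imbalance of one standard error shifts an unadjusted change-score estimate by (1 − r) × 2.86, which is 2.0, 1.4 and 0.9 points at the three correlations, against a target of 8. HADS-D absorbs part of this if it correlates with the baseline.

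**Rank test.** In the no-sex-effect runs, Mann-Whitney on change ranged from no loss to 6.5 points below the stated model (58.5% against 65.0% at r = 0.3 and HADS-D correlation 0.7). With the 4-point sex effect the largest loss was 8.6 points (53.7% against 62.3%).

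**The case against.** **The article condenses a fuller plan.** It does not call its covariate list closed. That is fair, but the article does choose change scores and does name covariates. An analyst following it would leave out baseline and sex. This is a stated choice that can be improved.

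**HADS-D already does some of the work.** This stands. A reader might set an unadjusted change score against baseline-only ANCOVA and get 62% against 80%, 76% against 87% and 93% against 96%. Neither side of that comparison is the planned model or the full replacement, and it overstates the gain. For the HADS total, HADS-D supplies 7 of the 14 items, so its baseline is partly adjusted for already. BAI, HADS-A and blood pressure have no such cover.

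**SD 7 may be the SD of change.** The article does not say which it is. If so, unadjusted change-score power is 76% at every r and the absolute powers above do not apply. The variance ratio (1 + r)/2 still does.

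**Confounding.** A reader might infer that the change-score comparison is confounded by baseline. Under randomisation it is not: the estimator is unbiased, and imbalance matters for precision and for reading the one realised trial.

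**Sex.** A reader might infer that omitting the stratification factor invalidates the test. It does not. A constant sex difference in level cancels in change scores, omission costs precision only if sex predicts change, and the error is conservative.

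**The non-parametric rule.** A reader might infer that the data will choose the primary method. The text does not establish this. The sentence sits in a paragraph that opens with single measures and comes before the repeated-measures sentence. Plots are used alongside the formal test, and some non-parametric methods do take covariates. The rank-test losses above are modest and come from normal data, where the switch would not usually be triggered.

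**A mixed model with baseline among the responses** could recover the lost information, but none is specified.

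**Conclusion.** The point holds as one of precision. The stated covariates omit the outcome's own baseline and the stratification factor. Adding both at 12 per arm raises power by roughly 8–13, 3–8 and 0–2 percentage points at r = 0.3, 0.5 and 0.7. This rests on SD 7 being cross-sectional, on no sex effect, and on an assumed correlation of 0.3–0.7 between HADS-D and baseline. The gain is larger if sex is prognostic and negligible once r reaches about 0.7. The documents support no claim of bias or inflated type I error.

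The normality rule is secondary. Its reach is ambiguous, and it conflicts with the age statement only if it extends to the primary and secondary comparisons and a standard rank test is used.

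**What to change.** State one model for each outcome: the follow-up score on group, the same outcome's baseline, sex and age, plus HADS-D if it is kept. Fit it as ANCOVA or within the mixed model already planned. Change scores can still be reported, because regressing change on group and baseline gives the same group effect as regressing follow-up on them.

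Say whether the normality rule covers the primary analysis. If it does, remove the switch, check the model's residuals, keep the adjusted model as primary, and add a sensitivity analysis that carries the covariates (bootstrap, permutation or rank ANCOVA).

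The cost is wording and one or two degrees of freedom: with 24 completers and a single follow-up score, residual degrees of freedom go from 24 − 4 = 20 to 24 − 6 = 18 if HADS-D is kept. BAI, HADS and blood pressure are measured at baseline (Table 1), and sex and age are recorded at screening (Study setting), so no new data are needed.

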## Patient and public involvement

A user representative ([name] [name]) participated in the planning phase of the project. She reviewed the study protocol and participant information materials, and provided advice on the feasibility and participant burden of the intervention. Although patients or members of the public were not directly involved in the design of the research question, user input has been important for clinical relevance and for planning future implementation of the findings.

## Discussion

Prior studies have found that physical exercise is beneficial for patients suffering from different types of psychiatric illnesses. Exercise may of course improve physical health but can also contribute to a reduction in psychiatric symptoms.

While prior studies have suggested that high-intensity training can lead to a reduction in anxiety, there is less evidence relating to the benefits of this type of intervention within the frame of mental health services.

Moreover, little is known about how high intensity training compares to low intensity training with respect to effects on anxiety levels in patients suffering primarily from anxiety disorders.

This is, to our knowledge, one of the first studies that compares these two different types of physical training for patients suffering from anxiety disorders.

Participants will be recruited by contacting those referred to the Study Hospital for outpatient treatment of anxiety and also by direct active recruitment through media.

Participants will undergo a thorough psychiatric and somatic examination to assess eligibility and to exclude those who may be physically unfit to participate. We will randomise the participants into a high-intensity training group and a low-intensity training group, in order to study whether the intensity of training is of importance to outcome in terms of reduced anxiety symptoms.

The duration (four-week intervention) was chosen based on feasibility within the clinical setting, but also previous evidence that high-intensity interval training (HIIT) can yield measurable psychological and physiological benefits within short timeframes [21]. This supports a short, structured and time-efficient design suitable for clinical practice.

Complete blinding is not feasible or possible in exercise interventions, as participants and trainers are aware of the training intensity. To minimise bias, however, the outcome assessor (study nurse) will be blinded to group allocation, and the exercise physiologist will not have access to any outcome data.

This study will add to the present-day understanding of the efficacy of physical training for people suffering from anxiety, and for the importance of physical training for mental health in general.

The knowledge generated by this study may directly impact the evidence towards developing targeted interventions and the self-management of anxiety disorders, and the knowledge will be of importance in developing recommendations for the treatment of patients suffering from anxiety disorders. Should the treatment prove effective, this will be a simple, convenient and low-cost treatment option for many people.

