## Outcomes

### Primary outcome measures

The primary outcome measure will be the degree of anxiety symptoms measured by the Hospital Anxiety and Depression Scale (HADS) [25] and the Beck Anxiety Inventory (BAI) [24] prior to the first (pre) and after the last (post) training session is completed.

The HADS is a questionnaire that measures self-report levels of some symptoms of anxiety and depression [25]. The instrument consists of 14 questions (items), of which 7 are related to anxiety symptoms (HADS-A) and 7 to depression symptoms (HADS-D). Each item is rated from 0 to 3, which gives a range of scoring from 0 to 42, with a score ranging between 0 and 21 for the anxiety (HADS-A) and depression (HADS-D) subscales. The HADS is one of the most commonly used self-report instruments for measuring anxiety and depression [29] and has demonstrated good reliability and validity and has sound psychometric properties [29]. A previous study found a minimal clinically important difference (MCID) between 0.5 and 5.57 for the HADS-D, and between 0.81 and 5.21 for HADS-A [30]. We will calculate total HADS scores and subscores for anxiety symptoms and depressive symptoms, respectively.

The Beck Anxiety Inventory (BAI) [24] is a questionnaire that measures self-report levels of some symptoms of anxiety. The instrument consists of 21 questions (items), and each item is rated from 0 to 3, which gives a range of scoring from 0 to 63, a higher score indicating increased symptoms. The BAI measures anxiety symptoms including muscle tension, dizziness, racing heart, nervousness, fear of dying, abdominal discomfort, face flushing, sweating, light-headedness, fear of the worst happening and a feeling of choking. The BAI is one of the most commonly used self-report instruments for measuring anxiety [31] and has demonstrated good reliability and validity and has sound psychometric properties [32]. We will calculate total BAI scores.

Both the Hospital Anxiety and Depression Scale (HADS) and the Beck Anxiety Inventory (BAI) will be applied. HADS allows comparability with both psychiatric and somatic populations, while BAI provides a more detailed assessment of somatic anxiety symptoms. Using both HADS and BAI increases sensitivity and also validity in assessing anxiety.

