#### Heart rate variability

Heart rate variability (HRV), derived from ECG recordings, will be applied as a physiological indicator of autonomic regulation and stress response. HRV provides an objective complement to the self-reported anxiety measures (HADS and BAI), which measure the participants’ subjective experience of anxiety symptoms.

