### Blinding

The study is not double-blinded, as this is not possible with the current intervention. However, the study nurse is blinded to the condition (high-intensity vs low-intensity), while the exercise physiologist is blinded to the scores on the outcome measures. Therefore, the study nurse does not know which condition the participants belong to, while the exercise physiologist has no insight into how the patients score on the various outcome measures.

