## Ethics and dissemination

The project complies with the relevant national regulations and institutional policies and will be performed following the Helsinki Declaration.

The trial is approved by the Data Protection Officer at the University Hospital of North Norway and the Regional Committee on Health Research Ethics (714458) and has been registered at ClinicalTrials.gov (NCT06881758). The protocol and the ClinicalTrials.gov registration together include all items specified in the WHO Trial Registration Data Set, except for trial results, which will be made available after study completion.

The participants will be informed of the study objectives, risks and benefits and must provide written informed consent before participation. Participants can stop participation at any time without giving an explanation.

The study findings will be disseminated through international and national peer-reviewed journals, at national and international conferences, and through media releases. The results will be submitted for publication irrespective of the study findings.

Any substantial changes (i.e. changes affecting participant safety, scientific validity, study procedures, or data protection) will be submitted to the Regional Committee for Medical and Health Research Ethics (REK North; approval no. 714458) for approval before implementation. Urgent safety measures may be implemented immediately and will be notified to REK without delay. Changes that affect data processing will be notified to the Data Protection Officer at the University Hospital of North Norway, and ClinicalTrials.gov (NCT06881758) will be updated.

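### Blinding the study nurse does not make the primary assessment blinded, because BAI and HADS are self-reported by participants who know their training intensity

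*Protocol article*

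**What the plan says.** The Blinding section says that the trial cannot be double-blind, that "the study nurse is blinded to the condition (high-intensity vs low-intensity") and that the exercise physiologist does not see outcome scores. The Discussion accepts that "participants and trainers are aware of the training intensity". It then continues: "To minimise bias, however, the outcome assessor (study nurse) will be blinded to group allocation".

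Under Primary outcome measures the two primary instruments are HADS and BAI. For the first: "The HADS is a questionnaire that measures self-report levels of some symptoms of anxiety and depression". The BAI likewise "is a questionnaire that measures self-report levels of some symptoms of anxiety". The section on heart rate variability describes both in the same way: "HRV provides an objective complement to the self-reported anxiety measures (HADS and BAI").

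Study setting gives the nurse one task for these scales, which is to help participants complete them. Under Ethics and dissemination: "The participants will be informed of the study objectives, risks and benefits".

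**The concern.** For a self-report scale, the person who assesses the outcome is the participant. The Discussion gives the title of outcome assessor to the nurse and offers the nurse's blinding as the answer to the bias it has just conceded. For the two outcomes that decide the trial, the assessor is someone the same paragraph says is not blinded.

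At stake is how the primary contrast is read. If participants expect more from one programme than from the other, their BAI and HADS answers can differ between arms for that reason alone, and the data cannot separate this from an effect of training. The Background gives one reason why expectations might differ: it says that high-intensity training is perceived as more effective. A reader who relies on the blinding statement could give the primary result the weight of a blind-assessed one.

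**Working it through.** **1. Who rates what, and whether that person is blinded**

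| Measure | Role | Who produces the value | Blinded to arm? | Source |
|---|---|---|---|---|
| BAI | Primary | Participant; nurse assists | No | Primary outcome measures; Study setting; Discussion |
| HADS | Primary | Participant; nurse assists | No | Same |
| Blood pressure | Secondary | Nurse at screening; follow-up measurer not stated | Yes, if the nurse takes it | Recruitment; Blinding; Table 1 |
| EKG / HRV | Secondary | Nurse records at screening; follow-up recorder not stated | Yes, if the nurse takes it | Recruitment; Heart rate variability; Table 1 |
| MINI | Screening and baseline only | Clinician | Baseline only, so not relevant here | Table 1; Study setting |

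Table 1 lists no anxiety rating by a blinded person after baseline. Even if the nurse's blinding is perfect, the primary contrast compares answers given by unblinded participants.

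**2. The plan's own figures (reproduced as background, not disputed)**

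Inputs from Sample size calculation: expected post-treatment BAI of 14 and 22, so a difference of 8; SD 7; two-sided alpha 0.05; power 80%.

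n per group = 2 × [SD × (z₀.₉₇₅ + z₀.₈₀) / difference]² = 2 × [7 × (1.960 + 0.842) / 8]² = 12.02

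This agrees with the stated 12 per group (24 in total) to rounding. With 20% attrition, 24 / 0.80 = 30, or 15 per group, as stated.

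**3. What a reporting shift would do (illustration)**

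The documents give no size for such a shift, so 1 to 4 BAI points is an assumption, shown as a range. The true difference is set to zero. The test is the two-sided 5% t-test named in the sample size section.

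Standard error = 7 × √(2/n), which is 2.858 for n = 12 and 2.556 for n = 15.
Non-centrality = shift / standard error, with 2n − 2 degrees of freedom (22 and 28).
Chance of p < 0.05 = probability that a non-central t with that non-centrality falls outside ± the critical value.

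| Shift (BAI points) | Share of planned 8 | Non-centrality, n = 12 | Chance of p < 0.05, n = 12 | Non-centrality, n = 15 | Chance of p < 0.05, n = 15 |
|---|---|---|---|---|---|
| 0 | 0% | 0 | 5.0% | 0 | 5.0% |
| 1 | 12.5% | 0.35 | 6.3% | 0.39 | 6.7% |
| 2 | 25% | 0.70 | 10.3% | 0.78 | 11.8% |
| 3 | 37.5% | 1.05 | 17.1% | 1.17 | 20.5% |
| 4 | 50% | 1.40 | 26.8% | 1.56 | 32.7% |

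The chance is larger with 15 per group because a fixed bias does not shrink as the sample grows, while the standard error does. The planned analysis uses repeated-measures or mixed models with baseline HADS-D and age as covariates, so its exact figures would differ. Adjusting for baseline variables does not remove a reporting shift that follows allocation.

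**The case against.** The strongest reply is that the article hides nothing. It says that double blinding is impossible, it concedes participants' knowledge in the sentence directly before the claim, and it calls both scales self-report. Minimising bias is also not the same as claiming a blinded primary outcome. That stands: a reader might infer that the open design is concealed, and the documents do not support this. What remains is that nurse blinding is offered as outcome-assessor blinding without saying that it does not reach the primary outcomes.

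Second, nurse blinding has real value. A nurse who does not know the arm cannot help with the forms differently by arm, and the physiologist's lack of access to scores is a further safeguard. This stands too, so it would be wrong to say that the protection is empty or covers physiological measures alone.

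Third, there are mitigations. The comparator is an active, supervised programme with the same eight sessions, and HRV is added as an objective complement. These may reduce differential expectation or help in reading the result. They do not turn BAI or HADS into blinded ratings.

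Fourth, the direction of any bias is not established. A reader might infer that participants are told high intensity should win. The Ethics section says only that they learn the objectives, and the Discussion frames the question neutrally as whether intensity matters. The consent text and news stories are not at hand. Contact time could even favour the control: 45 minutes per session against 10 + 4 + 5 = 19 minutes. The Background's remark on perceived effectiveness makes a difference between arms plausible, but it proves neither its presence nor its direction.

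Finally, the 1 to 4 point range has no source in the documents, and the calculation shows only what such a shift would do. This is correct, and the figures are to be read in that way.

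**Conclusion.** The point holds as a misattributed safeguard. The blinding statement names the nurse as outcome assessor, but both primary outcomes are assessed by participants who know their training intensity. Nurse blinding protects neutral help with the questionnaires and any nurse-taken measurements, and no more than that.

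The finding itself rests on the article's text and needs no numerical assumption. The numbers illustrate the stakes only. If expectation shifted BAI by 1 to 4 points between arms, with SD 7 and no true difference, the false-positive rate would be 6–27% at 12 per group and 7–33% at 15 per group instead of 5%. The documents do not show that such a shift exists, how large it is, or which arm it would favour. They therefore do not support a conclusion that the primary result will be biased towards high intensity. No figure in the protocol is wrong on this account. The open design cannot be undone, but the description should be corrected.

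**What to change.** 1. In Blinding and in the Discussion, state that BAI and HADS are rated by unblinded participants. Limit the nurse-blinding claim to neutral assistance with the questionnaires and to measurements that the nurse takes, such as blood pressure and EKG.
2. Word the primary conclusion as self-reported anxiety under known allocation.
3. For participants still to be enrolled or trained, have the written information and the trainers' communication present both programmes as active training, without saying which is expected to do better.

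The cost is a less favourable blinding statement and possibly a minor amendment to participant materials. Recruitment was due to end in March 2026, so the third change may reach few people; the first two do not depend on recruitment.

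A sensitivity analysis adjusted for a rating of expected benefit is not needed. A rating taken after allocation would be a post-randomisation variable, would be missing for those already enrolled, and in 24 to 30 people could not separate expectation from training effect.
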